**Figure 2 fig2:**
[figure not shown]
CONSORT-SPIRIT flow diagram. AA, acupuncture + auriculotherapy.

Patients assigned to an experimental treatment will undergo 10 sessions of AA in addition to conventional treatment for a total duration of 4 weeks. Those assigned to the control group will undergo only conventional treatment.

### Conventional rehabilitation

All professionals involved in the rehabilitation of enrolled patients will be blinded to the study’s arm. Regardless of the arm of the study, all patients will undergo a customization based on the rehabilitation team rehabilitation plan and will include speech and physiotherapy.

Dysphagia rehabilitation will consist in passive approaches, including postural adjustments (e.g., head flexion to facilitate airway protection), oropharyngeal and peri-oral sensory stimulation—tactile, thermal, or gustatory—to elicit or modulate swallowing reflexes (45, 46), respiratory and orofacial facilitation, and oral hygiene protocols to prevent aspiration-related complications. Whether applicable, active techniques, such as the Shaker maneuver (47), Chin Tuck Against Resistance (48) or specific swallowing maneuvers like the supraglottic swallow, effortful swallow and the Mendelsohn maneuver, will be used based on the level of collaboration reached during the three-month period of experimentation (see Figure 3).

**Figure 3 fig3:**
[figure not shown]
Intervention protocol. CV23, Conception Vessel 23; ST36, Stomach 36; ST44, Stomach 44; SI3, Small Intestine 3; LI2, Large Intestine 2; TB17, Triple Burner 17; V2–V3, 2° and 3° branches of trigeminal nerve.

### Intervention

Patients assigned to the intervention arm will receive a total of 10 combined AA sessions lasting 25 minute each, in addition to the conventional treatment mentioned above. In order to balance practical feasibility, patient tolerance and clinical relevance in the context of early in-patient intensive rehabilitation, the AA treatment protocol was designed taking into account both the operating model applied at the Regional Reference Center for TCM “Fior di Prugna” and the length of stay in intensive rehabilitation wards, where the average hospital stay is approximately 4 weeks. Each session will be performed with the patient supine in bed or seated in a wheelchair by the acupuncturist qualified by a school registered to the Italian Federation of Acupuncture Societies. Sterile disposable acupuncture needles will be used.

The acupuncture protocol includes somatic points based on their traditional indications in Chinese traditional medicine and their relevance to the neuromotor and autonomic dysfunctions underlying swallowing disorders. Zusanli (ST36) and Neiting (ST44), both on the Stomach meridian, for their roles in digestive regulation and inflammation control. ST36 is known for enhancing gastrointestinal function, modulating systemic inflammation, and supporting motor recovery, while ST44 may help reduce oral inflammation and sialorrhea (49). Lianquan (CV23), traditionally indicated for tongue and throat disorders and widely used to facilitate articulation and swallowing by targeting the suprahyoid and lingual muscles (50). Additional points will be selected based on individual needs: Houxi (SI3) for cervical spasticity; Yifeng (TB17) for mandibular tension or bruxism; Yintang (EX-HN3) for agitation and to promote treatment cooperation, and Erjian (LI2) for sialorrhea, due to its role in clearing internal heat and regulating fluids.

The auricular acupuncture protocol was developed based on neuroanatomical rationale and preliminary clinical evidence supporting the role of cranial nerve stimulation in swallowing rehabilitation. The selected points—Throat, Shen Men, Palate Area, and zones corresponding to the second and third branches of the trigeminal nerve (V2–V3)—were chosen to engage key sensory and motor pathways involved in swallowing control (50). Stimulation of the throat point—anatomically corresponding to the pharyngeal region and innervated by trigeminal branches—has been associated with facilitation of the pharyngeal reflex; randomized trials using magnetic pressure have demonstrated promising outcomes in poststroke dysphagia (51). The Palate Area is involved in the preparatory and oral phases of swallowing. Its proximity to zones innervated by the facial and trigeminal nerves supports its role in enhancing oral motor coordination and bolus transit. The V2–V3 auricular zones were included for their involvement in orofacial motor control, mastication, and sensory feedback from the oral cavity. Stimulating these areas may improve oral awareness and functional control during the early stages of swallowing. Shen Men, while not directly connected to oropharyngeal structures, was included for its autonomic and limbic modulatory effects. It has been shown to reduce stress and sympathetic overactivation, which can impair swallowing coordination, particularly in patients with cognitive or emotional dysregulation post-injury (52) (see Figure 3).

### Harms and adverse events

Expected adverse events (AEs) include mild pain, local bleeding or bruising at needle sites. Serious adverse events (SAEs) can include pneumothorax. All AEs and SAEs will be documented from randomization to the end of follow-up, with causality assessment by the investigator. No thoracic points will be used to prevent pneumothorax. To prevent the inadvertent retention of needles, the acupuncture physician will perform a systematic needle count at the end of each procedure.

### Adherence and co-interventions

Session attendance will be recorded. Participants missing >30% of sessions without medical justification will be considered non-adherent. Other neuromodulatory therapies (e.g., pharyngeal electrical stimulation, rTMS) will not be permitted during the trial.

### Discontinuation and modification criteria

Intervention discontinuation will occur in cases of clinical deterioration, adverse events judged to be treatment-related or withdrawal of consent by the legal representative.

### Outcome measures

The primary outcome is the improvement of dysphagia and will be measured using the MASA scale (53, 54) and the instrumental scale “Rationale scores based on endoscopic landmarks and bedside parameters” with relative values (43) at T1. The same scales will be used at T2 to measure the maintenance of the effect.

Secondary outcomes include: (1) improvement on the decannulation rate and/or reduction in decannulation timings at T1 and T2; (2) reduction of the rate of infections at T1 and T2; (3) improvement on functional autonomy measured by the GOS-E at T2.

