## Materials and methods

### Study design, setting and participants

This multicenter, longitudinal, randomized, controlled, patient- and assessor-blinded trial (ClinicalTrials.gov: NCT068882) aims to evaluate whether combining AA with standard logopedic therapy is superior to usual care alone for rehabilitating dysphagia in vascular sABI patients with a tracheal cannula. The protocol was developed in accordance with the SPIRIT 2025 (Standard Protocol Items: Recommendations for Interventional Trials) guidelines (37) and STRICTA (Standards for Reporting Interventions in Clinical Trials of Acupuncture) recommendations (38). Patients admitted to the IRU of the IRCCS Fondazione Don Carlo Gnocchi in Florence will be considered for screening. Eligibility will be determined based on predefined diagnostic, inclusion, and exclusion criteria as outlined below.

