### Statistical analysis

At present, we have designed a pilot study with the purpose of providing preliminary data necessary to calculate the appropriate sample size for a subsequent randomized controlled trial (RCT). The main study will be a 2-arm, randomized, controlled trial for which a medium effect size was conservatively hypothesized. According to the stepped rules of thumb proposed to estimate the size of the pilot based on Cohen’s d effect size (55), for an 80% power main trial, the pilot sample size should be 10 per arm, and the subsequent main trial will require somewhere between 34 and 176 participants per arm. The sample size of 10 participants per arm will be increased to 12 participants per arm to account for potential dropouts. This sample size was determined exclusively since methodological recommendations available in the literature. The data obtained from this pilot study will be used to estimate the effect size and variability, which will inform the power analysis and the determination of the required sample size for the definitive RCT. Analyses will be conducted using SPSS version 28 software (SPSS, SPSS Inc., Chicago, United States). The normality of the distribution of continuous variables will be checked using the Shapiro–Wilk test. If the variables violate the assumption of normality, they will be presented through their median value and interquartile range, otherwise through mean and standard deviation. Categorical variables will be represented through absolute frequencies and percentages. Baseline characteristics will be compared between treatment and control groups using independent *t*-tests or Mann–Whitney U tests for continuous variables, depending on data distribution, and chi-square or Fisher’s exact tests for categorical variables. The primary outcome (improvement in dysphagia) will be assessed by comparing MASA scores and “Pooling score” between groups at T1 using ANCOVA models (adjusting for baseline values) or non-parametric alternatives, if assumptions are not met. Maintenance of the effect at T2 will be evaluated using linear mixed models with random intercepts, including group, time (baseline, T1, T2), and their interaction as fixed effects; if model assumptions are violated, change scores between T1 and T2 will be calculated and compared between groups using independent *t*-tests or Mann–Whitney U tests. Secondary outcomes will be analyzed as follows: decannulation rates at T1 and T2 will be compared between groups using chi-square or Fisher’s exact tests, while decannulation times will be compared using independent *t*-tests or Mann–Whitney U tests and Kaplan–Meier survival analysis. Infection rates at T1 and T2 will be compared between groups using chi-square or Fisher’s exact tests. Functional autonomy at T2, measured by the GOS-E, will be compared between groups using independent *t*-tests if normality assumptions are met, or Mann–Whitney U tests otherwise. A *p*-value <0.05 will be considered significant in all analyses. The primary analysis will follow the intention-to-treat (ITT) principle. Sensitivity analysis will be performed to assess the robustness of the findings, including per-protocol analysis restricted to patients who completed the assigned intervention.

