The present study protocol has been carefully designed to consider not only the individual characteristics of dysphagia, the patient population, and the proposed intervention, but also the dynamic interactions among these three factors. An accurate assessment of swallowing function represents a critical step for monitoring the primary outcome namely the progression of dysphagia throughout the rehabilitation process. For this purpose, in addition to FOIS offering a crude description of dysphagia, the MASA, a bedside clinical scale for swallowing consisting of 26 items that can be easily administered by speech therapists, was chosen. This scale has demonstrated good psychometric properties in brain-injured patients with cognitive impairment (53) and has been used in tracheostomized patients (56). As is often the case with clinical scales, the reliability of the MASA can be reduced in non-communicative patients because some items—such as auditory comprehension, expressive communication, alertness, cooperation, command following, apraxia, articulation, oral preparation and transit, and respiratory-swallow coordination—can be challenging to administer. To mitigate this limitation, an instrumental evaluation by FEES to detect any changes—including subclinical ones—in swallowing function is included in this study. This dynamic endoscopic technique primarily evaluates the pharyngeal phase of swallowing—excluding the whiteout period—while also providing indirect information about the oral and esophageal phases. Furthermore, FEES allows for the targeted assessment of laryngeal sphincter function, sensory responsiveness, and the presence of pharyngeal residue. Its minimally invasive nature and feasibility for bedside application make it particularly suitable for patients in unstable clinical conditions (57). Given the complexity of these cases, which often involve reduced responsiveness and impaired postural control, FEES is strongly recommended both to guide the initiation of oral feeding rehabilitation programs (58, 59) and to support decisions regarding decannulation The Pooling Score, a clinical endoscopic evaluation will be used to assess the severity of swallowing disorders, considering excess residue in the pharynx and larynx (43). This score ranges from a minimum of 4 to a maximum of 11 and is calculated by summing the scores assigned to: Bolus location, Amount of residue, Ability to control residue/bolus pooling, assessed based on coughing, throat clearing (raclage), and the number of dry voluntary or reflex swallowing attempts (<2, 2–5, >5).

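### Two primary scales at T1 are each tested at unadjusted p<0.05, with no rule for what counts as success or which scale will size the main trial

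*Protocol article*

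**What the plan says.** Under Outcome measures, the protocol article states: "The primary outcome is the improvement of dysphagia and will be measured using the MASA scale". The sentence goes on: "and the instrumental scale “Rationale scores based on endoscopic landmarks and bedside parameters” with relative values", with assessment at T1. The endoscopic scale and the Pooling score are read here as the same instrument, because both carry the same citation.

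Statistical analysis describes the primary analysis as "comparing MASA scores and “Pooling score” between groups at T1 using ANCOVA models", adjusted for baseline, with non-parametric alternatives. It then sets one threshold for everything: a p-"value <0.05 will be considered significant in all analyses". No composite, testing order or alpha split is given.

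The article gives the study two roles. Study design, setting and participants says the aim is to see whether the combined treatment "is superior to usual care alone for rehabilitating dysphagia in vascular sABI patients with a tracheal cannula". Statistical analysis says "we have designed a pilot study with the purpose of providing preliminary data necessary to calculate the appropriate sample size" for a later trial, with 10 patients per arm raised to 12 for dropout.

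The Discussion says that "the reliability of the MASA can be reduced in non-communicative patients" and that the endoscopic examination was added to offset this. It attaches no decision rule to that reasoning.

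**The concern.** One primary outcome is served by two tests, each at 0.05, and the reader cannot tell which pattern of results would support the claim that dysphagia improved. This goes beyond detail left to an analysis plan: the article itself chooses two primary measures and fixes 0.05 for all analyses. A later plan that adjusted alpha would depart from that sentence.

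Two things are at stake. First, the error rate of the primary claim depends on a rule that could be chosen after the results are known. Second, the pilot is to deliver an effect size and a variability for the definitive trial, but the article does not say on which scale.

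Disagreement between the scales is foreseeable. The trial enrols only patients at LCF 4 or below, and the Discussion lists many MASA items as hard to administer in non-communicative patients.

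**Working it through.** **1. The plan's own figure.** Statistical analysis gives 34 to 176 per arm for a main trial with 80% power and a medium effect. With n = 2(1.96 + 0.8416)²/d² = 15.70/d², two-sided alpha 0.05:
- d = 0.3: 15.70/0.09 = 174.4, so 175 (exact t: 176).
- d = 0.7: 15.70/0.49 = 32.04, so 33 (exact t: 34).

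The stated range reproduces. The bounds 0.3 and 0.7 are assumptions solved back from the range, since the article gives no numeric effect size. The calculation concerns a single endpoint.

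**2. Inputs for the error rate.** There are two primary tests at T1 (Outcome measures), each at 0.05 (Statistical analysis). Assumed, because not stated: two-sided testing, and correlation ρ between the two test statistics.

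**3. False-positive rate with no effect on either scale.** For bivariate normal statistics:
- Either scale suffices: 1 − P(|Z₁| < 1.96 and |Z₂| < 1.96). At ρ = 0 this is 1 − 0.95² = 0.0975.
- Both required: 0.05 + 0.05 − P(either). At ρ = 0.5 this is 0.10 − 0.0907 = 0.0093.

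| ρ | Either, 0.05 each | Both, 0.05 each | Either, 0.025 each |
|---|---|---|---|
| 0 | 9.75% | 0.25% | 4.9% |
| 0.3 | 9.5% | 0.5% | 4.8% |
| 0.5 | 9.1% | 0.9% | 4.7% |
| 0.8 | 7.8% | 2.2% | 4.0% |
| 0.9 | 7.0% | 3.0% | 3.6% |

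If one scale has a real effect and the other none, a false joint success needs the null scale to be significant. The both-required rule therefore never exceeds 5%. With no effect on either scale, Holm has the same error rate as the last column.

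**4. Check at the pilot's size.** Simulated pairs of ANCOVAs with 12 per arm (20,000 runs each) gave, at ρ = 0, 0.5 and 0.8, 9.3%, 9.0% and 7.9% for either scale, and 0.3%, 0.8% and 2.0% for both. The normal results hold at this size.

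**5. Power.** For an assumed d = 0.5 on one scale and an unadjusted t-test, power is 18.5% with 10 per arm and 21.6% with 12. If both scales are required at 12 per arm, power lies between 0.216² = 4.7% (independent tests) and 21.6% (perfectly correlated tests).

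**6. Choosing the sizing scale afterwards.** Assume a true d of 0.5 on both scales, 12 per arm and unadjusted comparison. The standard error of d is about √(2/12) = 0.408. Taking the larger of two estimates raises d on average by 0.408 × √((1 − ρ)/π):
- ρ = 0: 0.23.
- ρ = 0.5: 0.408 × 0.399 = 0.163.
- ρ = 0.8: 0.10.

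At ρ = 0.5, sizing on d = 0.663 gives 37 per arm (exact t) instead of 64. With 37 per arm, power at the true d = 0.5 is about 56% instead of 80%.

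**The case against.** The strongest reply is that the text joins the two scales with a plain conjunction, so a both-required reading is at least as natural as an either-suffices one. On that reading no error rate is inflated. This stands. A reader might infer that the false-positive rate is nearly doubled, but that needs an either-scale rule, which the article never states, together with near-zero correlation. Both scales rate the same swallowing disorder in the same patients, so some positive correlation is plausible.

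The second reply is that this is a pilot. Its sample size comes from a rule of thumb and does not rest on alpha, and its stated output is an effect size and a variability. That lowers the severity but does not remove the point. The article also states a superiority aim, calls effectiveness its main purpose in the Discussion and relies on significance tests. Step 6 shows that the gap touches the pilot's own purpose as well.

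Two other inferences are tempting and do not hold. Counting about 11 planned between-arm tests gives 1 − 0.95¹¹ = 43%. But those tests share patients and time points, two of them are different methods on the same decannulation times, and no secondary result is made a success criterion. Nor does the Discussion settle on the Pooling score as the better primary measure. It also credits MASA with good psychometric properties in brain-injured patients with cognitive impairment and presents endoscopy as a complement. Randomization is stratified by MASA.

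**Conclusion.** The concern holds in a conditional form. Two primary scales are each tested at unadjusted 0.05, with no success rule and no reading for discordant results. If either scale suffices, the primary false-positive rate is about 7.0% to 9.75%, or 1.4 to 1.95 times the stated 5%. If both are required, it is at most 5%, at the cost of power. These figures rest on two-sided tests and an assumed correlation of 0.9 to 0.

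The unnamed sizing scale is a separate consequence, and for a pilot perhaps the more practical one. Its size in step 6 depends on an assumed d of 0.5 on both scales. Given the pilot status and 12 patients per arm, this is a should-fix.

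**What to change.** Before anyone sees outcomes by arm, write one rule into Outcome measures and Statistical analysis. Any of these would do:
- Name one primary scale, at the sponsor's choice, with the other as first secondary.
- Require both scales to reach 0.05.
- Keep both as primary and apply Holm: the smaller p-value against 0.025 and, if it passes, the larger against 0.05.

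Also name the scale whose effect size and variability will size the definitive trial. Limit the sentence that "will be considered significant in all analyses" to the primary comparison, and report T2 and secondary comparisons as estimates with 95% confidence intervals.

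The change takes a few sentences. The registry record was not available for this review, so the sponsor should check that it agrees. Naming one scale leaves alpha at 0.05. Holm brings a slightly stricter threshold for the smaller p-value, and requiring both lowers power as in step 5.

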### Statistical analysis

At present, we have designed a pilot study with the purpose of providing preliminary data necessary to calculate the appropriate sample size for a subsequent randomized controlled trial (RCT). The main study will be a 2-arm, randomized, controlled trial for which a medium effect size was conservatively hypothesized. According to the stepped rules of thumb proposed to estimate the size of the pilot based on Cohen’s d effect size (55), for an 80% power main trial, the pilot sample size should be 10 per arm, and the subsequent main trial will require somewhere between 34 and 176 participants per arm. The sample size of 10 participants per arm will be increased to 12 participants per arm to account for potential dropouts. This sample size was determined exclusively since methodological recommendations available in the literature. The data obtained from this pilot study will be used to estimate the effect size and variability, which will inform the power analysis and the determination of the required sample size for the definitive RCT. Analyses will be conducted using SPSS version 28 software (SPSS, SPSS Inc., Chicago, United States). The normality of the distribution of continuous variables will be checked using the Shapiro–Wilk test. If the variables violate the assumption of normality, they will be presented through their median value and interquartile range, otherwise through mean and standard deviation. Categorical variables will be represented through absolute frequencies and percentages. Baseline characteristics will be compared between treatment and control groups using independent *t*-tests or Mann–Whitney U tests for continuous variables, depending on data distribution, and chi-square or Fisher’s exact tests for categorical variables. The primary outcome (improvement in dysphagia) will be assessed by comparing MASA scores and “Pooling score” between groups at T1 using ANCOVA models (adjusting for baseline values) or non-parametric alternatives, if assumptions are not met. Maintenance of the effect at T2 will be evaluated using linear mixed models with random intercepts, including group, time (baseline, T1, T2), and their interaction as fixed effects; if model assumptions are violated, change scores between T1 and T2 will be calculated and compared between groups using independent *t*-tests or Mann–Whitney U tests. Secondary outcomes will be analyzed as follows: decannulation rates at T1 and T2 will be compared between groups using chi-square or Fisher’s exact tests, while decannulation times will be compared using independent *t*-tests or Mann–Whitney U tests and Kaplan–Meier survival analysis. Infection rates at T1 and T2 will be compared between groups using chi-square or Fisher’s exact tests. Functional autonomy at T2, measured by the GOS-E, will be compared between groups using independent *t*-tests if normality assumptions are met, or Mann–Whitney U tests otherwise. A *p*-value <0.05 will be considered significant in all analyses. The primary analysis will follow the intention-to-treat (ITT) principle. Sensitivity analysis will be performed to assess the robustness of the findings, including per-protocol analysis restricted to patients who completed the assigned intervention.

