### Randomization, allocation concealment and blinding

After enrollment, patients will be allocated to one of two groups by computerized randomization and stratified by MASA scale, with an allocation ratio of 1:1, and assigned to either the control or intervention arm. Allocation concealment will be ensured via sequentially numbered, opaque, sealed envelopes prepared by an independent statistician (see Figure 2). The study is designed as double-blind: all clinical and instrumental assessments will be performed by professionals blinded to the treatment arm, and patients are considered blinded either because they present a DoC or due to severe cognitive impairment with short-term memory deficits, which prevent them from being aware of or recalling the treatment received. Due to the nature of the acupuncture intervention, blinding of the acupuncturist is not feasible and represents a potential source of performance bias. To minimize its impact, several mitigation strategies were implemented *a priori*. Acupuncturists will not be involved in outcome assessment, rehabilitation planning, or data analysis. The intervention will be delivered according to a standardized protocol, including fixed session duration, predefined acupuncture points, and uniform treatment setting. Outcome assessors and the rehabilitation team will remain blinded to group allocation throughout the study. Any accidental unblinding will be documented.

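### The definitive RCT's power analysis is to draw on the effect size seen in a pilot of 10 to 12 per arm, an estimate with a standard error nearly as large as the hypothesised effect

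*Protocol article*

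**What the plan says.** Under Statistical analysis, the protocol article presents the study as a pilot that is to supply the data for sizing a later RCT. For that later trial "a medium effect size was conservatively hypothesized", with no numerical d given. A published rule of thumb is then applied, under which "for an 80% power main trial, the pilot sample size should be 10 per arm". The same rule is taken to give a range for the size of the definitive trial: "the subsequent main trial will require somewhere between 34 and 176 participants per arm". To allow for losses, "The sample size of 10 participants per arm will be increased to 12 participants per arm to account for potential dropouts".

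The section then turns to how the results will be used: "The data obtained from this pilot study will be used to estimate the effect size and variability, which will inform the power analysis". The same sentence extends this to the size of the definitive RCT. So both the treatment effect and the variability are to come from the pilot. The section names no minimum important difference or other fixed target effect. It also gives no allowance for the imprecision of the pilot estimates.

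**The concern.** A pilot of this size can give a rough SD. It cannot give a usable treatment effect, because sampling error in d is almost as large as the effect being looked for. The plan begins from a hypothesised medium effect and then proposes to let a much noisier number inform the calculation.

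Sizing the later trial is the pilot's declared purpose, so the sentence governs its main product. A pilot that is lucky by chance would point to a main trial far too small to answer the question. An unlucky one would point to an unattainable trial, or to none, even if the treatment has a worthwhile effect.

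**Working it through.** **Inputs.** From the protocol article: 10 evaluable and 12 enrolled per arm, 80% power for the main trial, significance at 0.05, allocation 1:1, main trial 34 to 176 per arm. Assumed: two-sided testing (not stated), and d = 0.5 for the medium effect with range 0.3 to 0.7.

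**1. The plan's own range.** n per arm = 2(1.96 + 0.8416)²/d² + 1 = 15.70/d² + 1, rounded up.
- d = 0.3: 174.4 + 1 = 175.4, so 176.
- d = 0.7: 32.0 + 1 = 33.0 (33.04 unrounded), so 34.
- d = 0.5: 62.8 + 1 = 63.8, so 64.

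Both stated bounds reproduce, which supports 0.3 to 0.7 as the implied range. The dropout allowance is 2 of 12, or 16.7%.

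**2. Precision of the pilot effect.** SE(d) ≈ √(2/n + d²/(4n)).
- n = 10, d = 0.5: √(0.2 + 0.00625) = 0.454.
- n = 12, d = 0.5: √(0.1667 + 0.0052) = 0.415.

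An observed d of 0.5 has a noncentral-t 95% CI of −0.40 to 1.38 at 10 per arm, and −0.32 to 1.31 at 12.

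**3. Pilots with no positive effect.** P(d ≤ 0) = Φ(−d√(n/2)). At 10 per arm with d = 0.5 this is Φ(−1.118) = 13%. It is 25% at d = 0.3 and 6% at d = 0.7.

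**4. Direct use of the observed d.** In 400,000 simulated pilots per scenario, each positive observed d went into the formula of step 1. The resulting trial's power was evaluated at the true d. At true d = 0.5, fewer than 32 per arm gives under 50% power. The formula returns that when the observed d is at least √(15.70/30) = 0.72. Percentages are of all pilots.

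| True d | Pilot per arm | Observed d ≤ 0 | Main trial under 50% power |
|---|---|---|---|
| 0.3 | 10 | 25% | 39% |
| 0.5 | 10 | 13% | 32% |
| 0.7 | 10 | 6% | 26% |
| 0.3 | 12 | 23% | 38% |
| 0.5 | 12 | 11% | 31% |
| 0.7 | 12 | 4% | 24% |

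At d = 0.5 and 10 per arm, the computed n has quartiles of about 22 and 145 to 149 across runs and rounding conventions, against a correct 64. It falls below 34 in 34% of pilots and above 176 in 19%. With Hedges' g in place of Cohen's d, the under-50% share is 30%.

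**5. Which figure reflects the small pilot.** At true d = 0.5, the share of pilots leading to power below 80% is 50% at 10, 50% at 50 and 49% at 200 per arm, so it does not depend on pilot size. The share leading to power below 50% does: 32%, 14% and 2%.

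**6. The alternative, with the effect fixed at 0.5 and only the SD taken from 10 per arm.** Used without a margin, the SD leaves about 53% of trials below 80% power but only 3% below 50%. With the one-sided 80% upper limit for the variance (×1.40 at 18 df), these become about 19% and 0.4%. The main-trial size would then be about 62.8 × 1.40 = 88 per arm.

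**The case against.** The strongest reply is that the text says only that the estimates inform the power analysis. It does not say that the raw d will be substituted into a formula. The same section states a prior range of 34 to 176 per arm. If that range were meant as a bound, and pilots with d ≤ 0 were sent to 176, no trial would fall under 50% power at d = 0.5, since 34 per arm already gives 53%. At d = 0.7 none would fall below 80%. This stands in part: the figures are conditional on direct use. But the article does not say that the range caps the result, and at d = 0.3 such a cap would still leave 39% under 50% power.

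Second, the definitive RCT will need its own protocol and sample-size justification, and could adopt a minimum important difference there. That is a fair reason to lower the severity. It does not make the stated plan a good one.

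Third, ANCOVA would be more precise than the unadjusted comparison simulated here. The baseline–T1 correlation is not given, and on the standardised scale the argument is the same.

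Two stronger readings are tempting but not supported. A reader might infer that the small pilot makes the main trial underpowered about half the time. The half is real, but it arises for any roughly median-unbiased estimate at any pilot size, and also when only the SD is borrowed. A reader might also infer that the plan takes the SD at face value. The article is silent on how the SD will be used.

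**Conclusion.** The point holds as a moderate one. Letting the pilot's effect size inform the power analysis is an explicit choice, and 10 to 12 per arm cannot support it. The harm specific to a small pilot is the depth of the possible shortfall and the chance of no usable answer. At an assumed true d of 0.5 and 10 per arm, just under a third of pilots lead to a main trial with less than 50% power, and 13% give no sample size at all. These figures rest on direct use of the observed d, two-sided testing at 0.05, normally distributed outcomes and an unadjusted comparison.

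It does not follow that the present trial is compromised. Its allocation, outcomes and analysis are untouched, and its variability data remain useful for planning.

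**What to change.** Replace the sentence on using the pilot's effect size and variability with text to this effect:
- The definitive RCT will be powered on a minimum clinically important difference, stated in advance on the scale chosen as its primary outcome.
- The pilot will supply only the SD, the baseline–T1 correlation and attrition.
- The sample size will allow for imprecision in the SD. An upper confidence limit is one way; the one-sided 80% limit multiplies the variance by 1.40 at 18 df or 1.35 at 22 df. Other margins are defensible.
- The pilot's treatment effect will be reported with its 95% CI and will not be the planning effect.

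The cost is a change of wording and the work of agreeing a minimum important difference. If an SD margin is used, the main trial grows, by about 35% to 40% with the example limit. The pilot's size and procedures stay as they are.
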